## Abstract

**Background:**

Due to the burden of musculoskeletal diseases in the elderly and the multifactorial nature of such conditions, controlling the pain caused by these disorders requires multidisciplinary approach. This approach requires the participation of the elderly in applying effective prevention measures. This study aims to design a multidisciplinary educational intervention based on health belief model (HBM) for elderly residents of nursing homes.

**Methods:**

This is a parallel randomized clinical trial among elderly people aged 60 years and over living in a nursing home who suffer from musculoskeletal pain. Eligible participants will be divided into two groups including the intervention group who will receive a multidisciplinary intervention (vitamin D consumption, psycho-social stress management, and physiotherapy) and the control group who will receive usual care. Data collection instruments will include demographic data, the Depression, Anxiety, and Stress Scale (DASS), the visual analogue scale (VAS), and a self-designed questionnaire containing the HBM constructs. The interventions will be carried out by the educational team (general practitioner, psychologist, physiotherapist, and health education specialist). Interventions include changing the wrong beliefs of the elderly, taking 800 units of vitamin D daily, daily walking exercise by the elderly for at least 30 min and maintaining proper body posture during daily activities, muscle relaxation, relaxation techniques, regular exercise, examining their diet and eliminating stimulants (such as smoking and coffee), regular visits with friends and family, and deep breathing techniques. All questionnaires will be completed by the elderly before, after, 3, and 6 months after the intervention.

**Discussion:**

The present study will evaluate the effect of an educational intervention based on a multifaceted pain control approach for elderly people who reside in nursing homes in order to reduce musculoskeletal pain in the elderly living in nursing homes. One of the features of this study is its focus on improving the health of elderly residents in nursing homes. Given the increase in the elderly population worldwide, the findings from the current trial might benefit elderly populations.

**Trial registration:**

IRCT20220904055881N1. Registered on 11 February 2023.

**Supplementary Information:**

The online version contains supplementary material available at 10.1186/s13063-024-08243-1.

## Background

Musculoskeletal disorders (MSDs) include over 150 diseases, which are characterized by conditions ranging from fractures, sprains, and strains to lifelong disabilities and usually with pain (often chronic), limited mobility, skill, and overall performance levels. Osteoarthritis, rheumatoid arthritis, osteoporosis, and other diseases are among the most common of these disorders [1–3]. Approximately 1.71 billion people have MSDs worldwide [2].

In 2022, there were 771 million people aged 65 years or over globally, 3 times more than the size in 1980 (258 million). The older population is projected to reach 994 million by 2030 and 1.6 billion by 2050 [4]. Iran has been argued that this country had the highest increase in the burden of MSDs over the past three decades worldwide [5]. Behavioral factors such as inactivity and repetitive movements, as well as non-behavioral factors such as aging, gender, and genetics, are involved these disorders [6]. Pain is one of the most noticeable symptoms of these disorders. Studies show that the elderly suffer from musculoskeletal pain [7, 8]. Inactivity [7], stress and depression [9], and vitamin D deficiency [10–13] can be mentioned among the causes of MSDs.

Control of MSDs in the elderly is crucial because it usually leads to disability and a reduction in their quality of life [14–16]. There are different types of methods for reducing pain, such as nutrition (vitamin D intake), physiotherapy, exercise, and stress management [12, 17–20]. Despite the proven effectiveness of many pain-reducing methods, adherence to these methods in old people is an important challenging issue due to disease characteristics and poor individual perception.

One of the inevitable changes of old age is cognitive and perceptual changes, which have negative effects on the quality of life of the elderly. One of the perceptual changes in the elderly that influences inactivity is the fear of falling [21]. Low self-confidence and low self-efficacy [21], as well as their lower knowledge and awareness [22] about the benefits of physical activity, is a big obstacle among elderly people. Different chronic diseases in old age is another issue [23] that could be contributed to inactivity in this age group. Immobility and movement phobia caused by fear, lack of knowledge about the benefits of vitamin D consumption, low income, and inability to buy and cook healthy food are among the reasons for vitamin D deficiency in old people [24].

Controlling and changing wrong beliefs in the elderly is essential, and there are various models which have been used, especially with the aim of reducing MSDs [25].

Considering the role of the individual’s perception in performing preventive behaviors, the health belief model (HBM) has been widely used to modify wrong beliefs in the elderly in order to change their behavior. This model emphasizes the role of modifying factors (demographic, psychological, characteristics personality and structural) and individual’s perceptions together in determining the probability of performing the behavior, which can be a very powerful combination to change the behavior [26]. According to this model, the adoption of health behavior is effective when a person believes in the benefits/barriers of preventive behavior to decrease his/her disease and also believes that he/she is susceptible to the disease which may be so severe and threaten [27]. The individual’s perception can have a positive or negative effect on doing preventive behaviors [28–30]. The lower perception of the behavior barriers as well as the higher self-efficacy causes the more preventive behaviors performing against these disorders [29]. In various studies, the relationship between self-efficacy [31] and understanding the benefits of exercise in preventing osteoporosis in women and ultimately reducing pain has been reported [32]. Moreover, the relationship between promoting self-efficacy regarding preventive behaviors of osteoporosis [28] and reducing barriers in promoting physical activity [33] has been proven. HBM-based empowerment program can be an effective strategy for increasing self-perceived efficacy and benefits and also reduce perceived barriers in the elderly regarding preventive behaviors [28, 34].

Due to the multifaceted nature of the factors affecting musculoskeletal pain, multidisciplinary approach management of these pains could be effective. The previous evidences argued that the preventive influential factors in MSD control include stress management, physical activity, and vitamin D intake which should be targeted in their interventional program design, and ultimately, should be educated through educational intervention for older adults it be resulted in reducing pain. This approach requires the participation of the elderly in improving their wrong behaviors and choosing effective prevention methods.

### Objective

Since in this regard, according to our knowledge, there is no multidisciplinary educational program based on a suitable model for solving MSDs in Iranian elderly, this study aims to design an educational intervention based on the health belief model with the aim of changing wrong beliefs and trying to perform the target behaviors according to the effective factors in causing pain (stress, vitamin D deficiency, and physiotherapy) is designed to reduce musculoskeletal pain in the elderly living in nursing homes in Tehran, Iran.

### Trial design

A parallel group randomized clinical trial will be conducted to assess the effectiveness of a health belief model based multidisciplinary intervention to reduce musculoskeletal pain in the elderly living in nursing homes. This protocol was developed and reported according to the recommendations of the Standard Protocol Items Recommendations for Interventional Trials (SPIRIT) [35], and will be conducted and reported following the Consolidated Standards of Reporting Trials (CONSORT) (Figs. 1, 2).

**Fig. 1 Fig1:**
[figure not shown]
The flowchart of the randomized controlled protocol

**Fig. 2 Fig2:**
[figure not shown]
The interaction of construct model and individual characteristics in performing behavior

## Methods

This study will be carried out in two phase as follows:Development and psychometric analysis of the study instrument

At this stage, a questionnaire will be designed based on the HBM constructs. Various statements will be included in the questionnaire based on previous studies on elderly musculoskeletal pain. The final instrument for analyzing the psychometric properties will be prepared (Table 1).

**Table 1 Tab1:**
[figure not shown]
Schedule of enrolment, multidisciplinary intervention, and assessment of the intervention following the Standard Protocol Items Recommended for Clinical Trials (SPIRIT) guideline

2.Conducting a clinical trial

### Study setting

The study will be carried in a nursing home in Tehran, Iran. There is evidence that usually a sample of people living in Tehran would be a representative of Iranian population [36, 37].

### Eligibility criteria

The inclusion criteria for participation in the study are being aged 60 years and above, elderly people suffering from musculoskeletal pain, being resident in nursing homes, and being able to perform physical activities and respond to questions. Exclusion criteria include elderly people with Alzheimer’s, mobility impairments, and individuals who use medication for pain control.

### Who will take informed consent?

The necessary coordination will be done by the health education specialist with the relevant organizations. After obtaining permission from the nursing home, the health education specialist is responsible for explaining the objectives of the study to the nursing home officials and also obtaining informed consent from the elderly participating in the study.

### Intervention

This is a multifaceted intervention to reduce the pain of the elderly by the intervention team (Table 2). The intervention team includes a general practitioner, psychologist, physiotherapist, and health education specialist.Physical activity would contain daily walking exercise by the elderly for at least 30 min and maintaining proper body posture during daily activities. Walking is done on a flat, un-sloped surface in their nursing home for half an hour. The proper posture of the body means a combination of the position of the different joints of the body relative to each other at the same time. The position of each joint will affect the position of the other joints. The proper posture is the position in which the least pressure is placed on the joints and the muscle activity is at its lowest level [38]. The proper posture involves proper position of the joints while standing, walking, sitting, and sleeping that will be laid in least stressed (to support muscles, joints, and ligaments during movement and activity). Sessions are held for 8 weeks, with three 1-h sessions per week, to maintain proper posture [39]. The training is done by the physiotherapist in the nursing home. First, how to maintain the correct body position and how to do it by the physiotherapist will be described, then he asks the elderly to perform the correct movements under the supervision of the physiotherapist to prevent injury. Films and posters are used for training as well as reminders.Vitamin D intake: A session will be given by the doctor in the form of a lecture about the benefits of vitamin D consumption for an hour. The doctor is obliged to answer the questions of the elderly. Each elderly person is given a daily dose of 600 to 800 IU of vitamin D tablets [40] for 6 months. One of the employees of the nursing home will be responsible for giving pills to the elderly daily. The doctor is obliged to answer the questions of the elderly during the intervention period.Psychological sessions will be conducted by a psychologist. Considering the conditions and facilities available, stress and depression reduction sessions should be carried out in such a way that all elderly people can benefit from them. These sessions include examining the elderly’s sleep, muscle relaxation, relaxation techniques, regular exercise, examining their diet and eliminating stimulants (such as smoking and coffee), regular visits with friends and family, and deep breathing techniques. These sessions are held by the psychologist for 8 weeks with 2 sessions per week, and each session lasts 90 min [41]. Training sessions in the nursing home will be conducted in the form of group discussions and proper training of techniques.Health belief model educational sessions will be held for changing the perceptions and beliefs of the elderly. After completing the self-designed questionnaire, training sessions are determined for each constructs. Training is done according to the type of constructs. Training sessions include group discussion, use of role models, increasing self-efficacy, etc. Meetings are held in the nursing home for 1 h, if the elderly wish, the meeting time can be extended. Considering that the model constructs target intervention behaviors in addition to the belief of the elderly, the presence of a health education specialist in other meetings is necessary.

**Table 2 Tab2:** Multidisciplinary intervention to reduce musculoskeletal pain based on the health belief model

Item	Intervention
Educational content	A series of videos and posters to teach proper body posture during daily activities, stress control and how to take vitamin D
Time line	Sessions are held for 8 weeks, with three 1-h sessions per week, to maintain proper posture. 8 weeks with 2 sessions per week, to control stress
Component	Health belief model constructs aimed at reducing perceived sensitivity, perceived severity and perceived barriers, increasing self-efficacy and perceived benefits and knowledge
Methods	Based on the constructs of the HBM model, various methods such as lectures, group discussions are used
Responsibilities	All team members are present during the intervention period. After the end of the intervention period, one of the staff members of each center will check the steps of the interventions and the adherence of the elderly to the interventions and send the relevant reports to the health education expert on a weekly basis. The team doctor and health education specialist will periodically meet with the elderly

### Strategies to improve adherence to interventions

As a reminder, one of the staff of the nursing home communicated with the intervention group and reminded them to do the interventions regularly. The health education specialist periodically monitors the implementation and maintenance of the interventions after the completion of the interventions. Finally, a reminder training will be provided for the intervention group after 3 months. The control group will not receive any intervention, but a training package will be provided to them after the study ends.

### Provisions for post-trial care

Considering the vulnerability of the target group, all health aspects of the plan are considered in all stages and possible complications are evaluated. The presence of a doctor in all meetings is necessary. Moreover, all participants are asked to report any possible side effects to be assessed by physician.

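### Harms rest on doctor-attended sessions and spontaneous reports, but tablets outlast the dated sessions, the later weekly report has no stated side-effect content, and the two arms are not observed alike

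*Protocol article*

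**What the plan says.** All references are to the protocol article.

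- **Provisions for post-trial care** holds the safety arrangement: "The presence of a doctor in all meetings is necessary. Moreover, all participants are asked to report any possible side effects to be assessed by" a physician. The sentence before it commits the team to evaluating complications at every stage, without method or timing.
- **Intervention** dates two sets of sessions: "Sessions are held for 8 weeks, with three 1-h sessions per week, to maintain proper posture" and "These sessions are held by the psychologist for 8 weeks with 2 sessions per week, and each session lasts 90 min". It adds one vitamin D lecture by the doctor and health belief model meetings that carry no dates or number.
- **Intervention** also gives "vitamin D tablets [40] for 6 months", with this arrangement: "One of the employees of the nursing home will be responsible for giving pills to the elderly daily". Walking is daily, with no stated duration in weeks or months.
- **Table 2 (Responsibilities)**, repeated in **Recruitment**, says that once the intervention period is over a staff member reviews whether each step is being followed. The object of the check and the reporting line are given in these words: "adherence of the elderly to the interventions and send the relevant reports to the health education expert on a weekly basis". Both places add that the team doctor and the health education specialist meet the residents periodically.
- **Strategies to improve adherence to interventions** adds one reminder training for the intervention group after 3 months. The control group receives nothing until the study ends.
- **Outcome measures** lists the pain scale, DASS-21, the health belief questionnaire, demographics and a behaviour questionnaire. None is described as recording falls, injuries or side effects. Assessments are before, immediately after, and 3 and 6 months after the intervention.
- **Blinding** states that the trial is not blinded.

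**The concern.** The safety arrangement has two parts: a doctor in the room, and residents who speak up after a general request. The first is tied to meetings, and the dated meetings stop well before the tablets do. The second is spontaneous reporting, which depends on how often a resident has an occasion to report and someone to report to.

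After the dated sessions, the only reporting with a stated frequency is the weekly staff report. As described, it asks about adherence, and its recipient is not the person who assesses side effects. A fall, an injury or a tablet complaint could be known to home staff and still have no stated path to the physician.

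The second problem is comparability. One arm is brought together with a doctor many times; for the other, no such meeting is stated. With spontaneous reporting, the arm that is seen more often tends to report more, whatever the true rates. A difference in reported harms, or the lack of one, could not then be interpreted. This matters because the article stresses the vulnerability of its participants and supervises the posture movements to prevent injury. Its Background also says: "One of the perceptual changes in the elderly that influences inactivity is the fear of falling".

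**Working it through.** The plan states no figure for this point, so there is none to reproduce. The check is a count of contacts, a share of time, and a reading of the passages side by side.

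**1. Dated sessions with a doctor present, intervention arm** (Intervention; Table 2)
- Posture: 8 weeks × 3 per week = 24
- Stress and depression: 8 weeks × 2 per week = 16
- Subtotal: 24 + 16 = 40
- Vitamin D lecture: 1, giving at least 41

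This is a minimum, because the health belief model meetings have no stated number. For the control arm, no such meetings are stated.

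**2. Share of the tablet period after the dated sessions**

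Assumption: tablets start with the sessions. The article gives no start date for either.

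Share after = 1 − (session weeks / tablet weeks)
- 6 months as 26 weeks: 1 − 8/26 = 18/26 = 69%
- 6 months as 24 weeks: 1 − 8/24 = 16/24 = 67%

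No such share can be computed for walking, since its duration is not given.

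**3. What is stated for the time after the dated sessions**

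| Contact | Frequency | Harm content | Reaches the physician? | Arm |
|---|---|---|---|---|
| Weekly staff report | Weekly | None stated (steps, adherence) | Not stated; goes to the health education specialist | Those following the interventions |
| Doctor's periodic meetings | No interval | None stated | Yes, by presence | Not stated |
| Reminder training | Once, after 3 months | None stated | Only if it counts as a meeting | Intervention |
| Follow-up questionnaires | Immediately, 3 and 6 months after | None described | Not stated | Both |
| Residents' own reports | When they occur | Side effects | Yes | Both |

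Only the last row has stated side-effect content.

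**4. The undefined intervention period**

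The weekly report starts when the intervention period ends, and that period is not defined.
- If it is the 8 weeks of sessions, the report covers the later tablet weeks, but for adherence only.
- If it is the 6 months of tablets, the report starts when the tablets stop. Table 2 would then have the whole team, doctor included, present throughout the tablet months, but no record of harms is described for that time either.

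On neither reading does a stated record collect harms during the tablet period, and on neither are the two arms asked the same question.

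**The case against.** The strongest case on the other side is that this is a condensed article. Adverse-event forms, contact intervals and reporting routes commonly sit in the full protocol, and the schedule in Table 1 is not shown. The passages are sparse but do not contradict one another. The article plans no safety outcome and no between-arm comparison of harms, so no planned result is biased. The Background mentions fear of falling as a barrier to activity, not as a hazard of the programme.

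Much of this stands, and it rules out several stronger readings that a reader might infer:

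- *That no doctor sees residents after week 8.* Not supported. Table 2 and Recruitment state periodic meetings, and the reminder training may be a meeting at which a doctor is required. The health belief model meetings are undated, so the text does not fix when all meetings end.
- *That reporting is unprompted.* Too strong. All participants are asked to report, and a physician assesses what they report. What is lacking is scheduled questioning.
- *That walking also runs for 6 months.* Only the tablets carry that duration.
- *That control residents never meet a doctor.* Not established. The request to report covers all participants, the periodic meetings are not limited to one arm, and controls complete the assessments. The description of the pain scale mentions a doctor measuring the line, though that may be a generic account of the scale. Controls take no trial tablets, so the issue in that arm is comparability, not unmonitored exposure.

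The objection does not remove the core. The article does not merely leave harms collection to another document. It states a method: doctor at meetings, general request to report, and a weekly report with named content and a named recipient. That stated method is passive and gives the arms unequal opportunity to report.

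**Conclusion.** The point holds as a recommended improvement. It is not an error in the primary analysis.

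The size is about two thirds of the tablet period (67% to 69%) after the dated sessions, and at least 41 dated doctor-attended meetings in the intervention arm against none stated for control. The share assumes that tablets start with the sessions, and it counts only the dated posture and stress sessions. The contrast in meetings counts what the article states. It does not prove that control residents have no contact with a doctor.

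As written, spontaneously reported harms could describe what came to light, but they could not support a statement that one arm had more or fewer harms than the other. That limit would matter as soon as the results paper comments on the safety of the programme.

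**What to change.** 1. Add fixed lines to the existing weekly staff report: fall, injury, new symptom, transfer to hospital, tablets stopped and the reason. Start the report at the first tablet and continue to the last tablet or the last visit, whichever is later. Copy it to the team doctor as well as the health education specialist.
2. At the three existing follow-up questionnaires (immediately, 3 and 6 months after), put the same short question on harms and falls to both arms. Base any between-arm comparison of harms on those answers only. Report events from the weekly report and from sessions descriptively.

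The cost is a few lines on a report, a second recipient, slightly more work for home staff and a slightly longer questionnaire. No extra staff or visits are needed, and no dose, schedule or clinical rule changes. If the full protocol already contains such a form and question, a sentence in the article pointing to them would settle the matter.
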